#### Analytical challenges and solutions.

##### Leader and implementation team analysis:

A primary challenge for this analysis is the non-random selection of the sample and relatively small sample sizes across the LIS and HIS groups. These limitations require the analyses to be largely descriptive and inferences to be restricted to the samples rather than to the university populations from which the samples are drawn. Still, our mixed-methods study design will allow us to triangulate findings from the qualitative and quantitative data collected from the university leaders and implementation teams, and both sets of findings with those from university faculty. This multi-method, multi-sample approach will permit a more nuanced understanding of the institutional changes that may be underway and that may facilitate or inhibit the implementation of GlobalConsent and/or planned implementation strategies. Thus, all findings from our approaches to Aims 1 and 2 will inform interpretation of the results for the implementation effectiveness assessment (Aim 3).

##### University faculty analysis.

DD methods provide unbiased effect estimates if the trend over time would have been the same between the treatment (HIS) and comparison (LIS) groups in the absence of the more intense elements of HIS implementation. However, selection bias may arise if the composition of these groups changes over time, such that the faculty population at participating universities changes systematically, for example, through substantial turnover or consolidation. One approach to address this issue is to restrict the sample of faculty to those who are available across all three survey waves and study years (1, 3, 5). If high turnover risks a substantial loss of power using this approach, we will consider the use of propensity score weighting to handle this type of confounding across four groups (HIS pre, HIS post, LIS pre, LIS post) [85] Another challenge in this analysis is the cluster-randomized design, where six universities are assigned to HIS or LIS groups. We will assess the robustness of our DD findings across a range of small-sample corrections, and we will report the methods used and findings to ensure transparency and reproducibility [86, 87].

##### Male student analysis.

1) We will include the age-standardized male student population in person period as an offset variable to convert the outcome into a rate and adjust for potential changes in the population over time. 2) We will consider methods to adjust for seasonality [88] or other time-varying confounders [89], such as concurrent training programs or changes in COVID-related conditions that alter opportunities for in-person versus online interactions at participating universities. 3) We will diagnose and address potential issues of over-dispersion [88] and residual auto-correlation [90, 91], and 4) we will conduct sensitivity analyses to test the impact of varying model specifications, such as whether a negative binomial regression model fits the data better than a Poisson regression model or different lags in slope changes for behavior and different impact models (e.g., non-linear trend model, school-year fixed effects model) [88, 89, 92, 93] 5) Another potential concern in CITS analyses of self-reported sexually violent behavior is systematic biases in reporting, including over time due to the repeated measurement of this sensitive behavior. Increased under-reporting over time could lead to falsely attributing declines in sexually violent behavior to the implementation of GlobalConsent. However, increased under-reporting due simply to the repeated measurement of sensitive behavior should not differ across LIS and HIS groups, such that estimates of differences in implementation effectiveness across groups should not be biased. Also, a review of survey experiments suggests little difference in reports of frequency of sensitive behaviors using standard interview methods versus month-by-month reporting [94]. Still, we will use various strategies shown to improve the reporting of potentially sensitive behaviors, including computer-assisted self-interview, assurances of anonymity, the choice for men to complete surveys in a private location of their choosing, and the use of multiple response options to capture the frequency of reported behaviors [94].

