#### First-year male students (Aims 1 and 3).

Eligible student participants will be male (sex assigned at birth), 18–24 years old at first contact, self-identified as heterosexual or bisexual (are attracted to women) and matriculating into the study universities in project year 2.

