As a first step in the analysis, we will inspect pretreatment data closely to select the modeling approach that best fits the data. Given the multi-module nature of GlobalConsent and evidence from the efficacy trial [51], we expect to see immediate level changes (improvements) in all outcomes at the first post-test survey and slope changes for all outcomes, as cognitive, attitudinal, affective, and behavioral change attenuate *partially but not entirely* [51]. We expect to see greater immediate improvement and less attenuation in the HIS group than the LIS group. A basic CITS model for the frequency of men’s sexually violent behavior may take the following form: log(E(Y_ijt_)) = B_0_ + B_1_T_t_ + B_2_Z_j_ + B_3_P_t_ + B_4_T_t_*HIS_ij_ + B_5_P_t_*HIS_ij_ + v_ij_, where Y_t_ is the outcome for the i^th^ participant for the j^th^ university at time t, B_0_ is a constant term showing the average frequency of sexually violent behavior in the reference university before implementation; Z_j_ is a vector of university dummies to allow a separate intercept for each university; T_t_ is the time elapsed since study start, where t=1,…,10 quarters; B_1_ is the pre-implementation trend in the comparison (LIS) group, and Β_1_ + B_4_ is the pre-implementation trend in the HIS group; P_t_ is a vector of indicators for each post-implementation time period; B_3_ is the level change in the reference university in the post-implementation period; v_ij_ is the random effect for the i^th^ participant at university j which would allow random subject-to-subject variation in the intercepts at each university. The difference in the actual post-implementation performance from the projected post-implementation performance in the HIS group, less this same difference in the LIS group, is the estimate of HIS effects (B_5_). This formulation assumes that all universities in the HIS group share the same trend, and all universities in the LIS group share the same trend (though possibly different from the HIS trend). This assumption could be relaxed by modeling the trends as random effects. To assess whether the slope of performance changes after implementation, we may code P_t_ as a dichotomous variable that equals 0 in the pre-implementation period and 1 in the post-implementation period. The change in slope can then be estimated by adding a three-way interaction between the higher-intensity implementation indicator (HIS_ij_), post-implementation indicator (P_t_), and linear time trend (T_t_). In this formulation, P_t_ would be coded to be centered on the introduction of implementation, so B_5_ is interpreted as the immediate shift in outcomes following implementation. Inclusion of this interaction would allow implementation effects to grow or decline over time. A similar CITS model will be applied to investigate the impact of GlobalConsent on the incidents of men’s prosocial intervening behavior in the two implementation-strategies groups.

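### The student-level model of each man's own count is given a male-population offset, so changes in a headcount over time enter its coefficients; the HIS effect itself is biased only by a step or curved change that differs between arms

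*Protocol article*

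**What the plan says.** Three parts of the protocol article bear on this.

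- **Analysis of quantitative data from students (Aim 3)** sets the unit as the person: "Y_t_ is the outcome for the i^th^ participant for the j^th^ university at time t". The basic equation is "log(E(Y_ijt_)) = B_0_ + B_1_T_t_ + B_2_Z_j_ + B_3_P_t_ + B_4_T_t_*HIS_ij_ + B_5_P_t_*HIS_ij_ + v_ij" and contains no offset. The last term is a "random effect for the i^th^ participant at university j which would allow random subject-to-subject variation in the intercepts". University size is handled only by fixed intercepts: "Z_j_ is a vector of university dummies to allow a separate intercept for each university".
- **Male student analysis**, under Analytical challenges and solutions, states: "We will include the age-standardized male student population in person period as an offset variable to convert the outcome into a rate". A second purpose is given, to "adjust for potential changes in the population over time". The commitment is firm; the next item in that list, on seasonality, is only to be considered.
- **Eligibility criteria** define one cohort, men "matriculating into the study universities in project year 2". It is surveyed three times before and three times after the 12-week delivery period.

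The section on power for student data simulates the same person-level model (repeated counts with a random intercept) at an incidence rate ratio of 0.825. Nowhere does the protocol say that student outcomes are summed to university totals.

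**The concern.** An offset enters a log-linear model with its coefficient fixed at 1. A population offset is right when the outcome is the total number of incidents in a university and period. Here the outcome is one man's count, which is already per person. The only natural exposure for it is the time over which he reports.

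Dividing his count by a headcount makes the model describe something other than his behaviour. The university dummies remove constant differences in size but not changes over the six waves. Both primary outcomes are affected, because a similar model is planned for prosocial intervening behaviour. The cost-effectiveness section takes the same between-arm contrast as its net effectiveness, so a bias in that contrast would pass into the ICER.

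**Working it through.** **The plan's own figures.** 0.65 + (1 − 0.65)/2 = 0.825, and 4,776 × 0.80 × 0.90 = 3,439. Both reproduce. The design log effect is |ln 0.825| = 0.192, which is the yardstick below.

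**Algebra.** Let μ be a man's true mean count and N_jt the offset population of university j at wave t. With the offset the model fits

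log μ = (linear predictor) + log N_jt, so (linear predictor) = log μ − log N_jt.

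With behaviour fixed, the linear predictor must reproduce −log N_jt. Each part of log N_jt goes to the term with the same shape:

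- constant size: the university dummies, no harm;
- a trend common to both arms: B1;
- a step at implementation common to both arms: B3;
- a log-linear trend that differs by arm: B4;
- a step or curvature that differs by arm: B5.

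**Numerical check.** A noise-free Poisson fit of the published equation used six waves, the Table 1 sizes, an assumed allocation within the regional pairs, and log population as offset. The participant intercept was left out; it does not change the mean structure here. All population changes are assumptions.

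| Assumed change in the offset population | Result with P coded 0/1 |
|---|---|
| None | no bias |
| 10% fall at implementation, both arms | level change 1.111; HIS IRR stays 0.825 |
| 5% step fall, HIS only | HIS IRR 0.825 becomes 0.868 |
| 10% step fall, HIS only | 0.825 becomes 0.917; 1.00 becomes 1.111 |
| 17.5% step fall, HIS only | 0.825 becomes 1.00 |
| 10% step fall, LIS only | 0.825 becomes 0.743; 1.00 becomes 0.900 |
| Constant-rate loss, 15% HIS against 5% LIS by wave 6 | false trend interaction 1.022 per wave; P*HIS 1.000 |
| Straight-line loss to the same end points | P*HIS 1.000 |
| Front-loaded loss to the same end points | P*HIS 0.991 |

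The trend figure follows by hand: (0.95/0.85)^(1/5) = 1.022.

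The article's basic form uses separate indicators for each post-implementation period. With that coding and no true effect, constant-rate loss again gives 1.000 and straight-line loss gives 1.002 to 1.007. One front-loaded pattern gives 0.974, 0.945 and 0.913 at the three post-implementation waves. Curvature can therefore matter more under this coding; the exact values depend on the assumed shape.

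**Step bias against the design effect.** False IRR = 1/(1 − f) for a step fall f in HIS only:

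- f = 5%: 1.053; 0.051/0.192 = 27%
- f = 10%: 1.111; 0.105/0.192 = 55%
- f = 15%: 1.176; 0.163/0.192 = 84% (from unrounded values)

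A 10% step in LIS only gives 0.90, the same 55% in the other direction.

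**Without the offset** the same set-up returns HIS IRR 0.825, level change 1.000 and trend 1.000, whatever happens to enrolment.

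**The case against.** The strongest reply is that the model already contains T and T*HIS. Men leaving at different steady rates in the two arms is close to log-linear, so B1 and B4 take it up and B5 does not move. That is correct, and the check above confirms it. A reader might infer that any change in enrolment, or any difference in the speed at which the cohort shrinks, creates a false HIS effect. The published equation does not support that. A reader might also take the 55% as an expected size. It is a worst case for an abrupt 10% differential exactly at implementation, and the protocol reports no enrolment trend of any kind. The 90% retention it assumes is survey retention, not a population change.

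Two further points have some weight. The equation is offered as a form the model may take after pretreatment data are inspected, and sensitivity analyses of the specification are planned. But the offset sentence is itself a firm commitment, and the listed sensitivity analyses do not mention it.

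The wording about person period is also unclear and might mean individual person-time. That does not fit an age-standardised population or the stated aim to "adjust for potential changes in the population over time". The sentence does not say whose population is counted (the university's men or the cohort), but any headcount has the same defect.

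**Conclusion.** The two sections describe incompatible models, and the offset sentence is wrong as written for a person-level count. The conflict is in the text and needs no assumption.

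Its effect on results depends on how the counted population moves. With a constant population there is none. Common changes corrupt the estimated level change and trend after implementation, which the protocol also intends to interpret, but leave the between-arm ratio alone. Differential steady change corrupts the trend interaction. B5 and the ICER are biased only by a differential step or curvature: up to 55% of the design log effect for an assumed 10% step, and about nothing for steady loss of similar size. The documents do not show which case applies.

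**What to change.** Delete the population offset from the student-level model. If reporting periods differ in length between men or waves, use the log of each man's own reporting time as the offset; the protocol article does not state a recall period, so this should be settled in the same edit. Cohort loss can stay with the mixed model and the planned imputation analyses.

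If an aggregate university-by-wave analysis was intended, state it as such and use the number of respondents as denominator. With 80% participation and 90% retention, reports come from 4,776 × 0.80 = 3,821 men at the start and 3,439 at the end. A fixed population denominator would count the missing men as having no incidents and show a 10% fall from non-response alone.

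The cost is one sentence. No data collection changes, and the power calculation as described already uses a person-level model with no population offset mentioned.

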#### Incremental cost-effectiveness analysis (Aim 4).

The cost-effectiveness analysis will be conducted from the payer’s perspective. Program costs will be calculated using a micro-costing approach, multiplying resource use by unit costs. Costs will be divided into the following two components based on the process necessary to set up and deliver the GlobalConsent program: 1) set-up costs (e.g., initial training costs, and set-up before the start of the program), and 2) program delivery costs (e.g., session time, preparation time, administrative costs, and materials/supplies). Cost data will be cleaned and used to estimate the total costs, set-up costs and program delivery costs per participant for each of the two groups (HIS vs LIS).

Net costs (the net increase in costs from the HIS vs LIS) and net effectiveness (the difference in the actual post-implementation performance from the projected post-implementation performance in the HIS group, less this same difference in the LIS group) will be used to calculate an incremental cost-effectiveness ratio (ICER) (costs per additional incident of sexually violent behavior averted or costs per additional incident of prosocial intervening behavior increased). Bootstrapping techniques will be used to conduct uncertainty analyses to assess variability in our findings from potential sampling bias.

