#### Incremental cost effectiveness outcomes (Aim 4).

The primary effectiveness outcomes for the cost-effectiveness analysis will be the frequency of sexually violent behavior and prosocial intervening behavior. The costing items are organized sequentially based on the implementation phases: pre-implementation, implementation, and post-implementation. Each phase includes a detailed list of activities (Tables 2, 3), with costs related to personnel, travel, space, and supplies/equipment collected for each activity. We will estimate the aggregate costs for each university and then divide this aggregate by the total number of participants at that university to determine the cost per participant.

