## Assignment of interventions: allocation

### Sequence generation {16a}

All universities in the sample are broadly matched on programs of study (health sciences) and are pair-matched on region (North, Central, South). Within matched pairs, universities will be randomized using a computer random number generator to receive ‘lower intensity’ (LIS) or ‘higher intensity’ (HIS) implementation strategies to deliver GlobalConsent to eligible undergraduate men.

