#### Costing surveys (Aim 4).

Cost elements for activities involving CCIHP staff and university implementation team members are detailed in the **Appendix**. The costing items for CCIHP should be completed monthly for each CCIHP staff member involved in the GlobalConsent intervention activities. For university implementation teams, costing items should be completed monthly outside the 12-week program implementation period and weekly during the 12-week program implementation period for each team member involved. CCIHP will collect all costing forms monthly outside the 12-week program implementation period and weekly during the 12-week program implementation period, de-identify the data, and then send the forms to the health economist for cleaning and analysis.

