#### Cost data (Aim 4).

The completed costing forms will be checked for consistency and missing information upon receipt. If any inconsistencies or missing information are found, the forms will be returned to CCIHP or the specific university via CCIHP for correction. Once the forms are verified as complete, they will be stored with a unique university ID and personnel ID in a folder accessible only to the health economist.

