
#### Power for analyses of student data (Aim 3).

We estimated the power to test models that tested for differences in the frequency of sexually violent behavior and prosocial intervening behavior between LIS and HIS groups. Using estimates for the mean frequency of sexually violent acts in the GlobalConsent Trial [51], we computed the statistical power with a generalized linear mixed model with a random intercept for repeated count measures via a simulation. We used the Stata command (ipdpower, model 2, a simulations-based command that calculates power for mixed-effects modeling with random effects for intercept) to perform the simulation. With a retained sample size of ~3,439 men (4,776 X 0.80 participation X 0.90 retention the final wave; ~1,719 in each implementation group), six counts for the frequency of sexually violent acts, an incidence rate ratio of 0.825 (0.65+(1–0.65)/2) for the rate of change after implementation of GlobalConsent for the HIS group relative to the LIS group, alpha level of .05, and 5000 simulations, estimated power was .91.

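### Aim 4 leaves uncertainty to an unspecified bootstrap, but net cost rests on three cost values per arm, and the standard bootstraps understate its uncertainty beyond these six universities

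*Protocol article*

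**What the plan says.** - **How cost per participant is built** (Outcomes {12}, Incremental cost effectiveness outcomes): "We will estimate the aggregate costs for each university and then divide this aggregate by the total number of participants at that university".
- **How it is summarised** (Statistical methods {20a}, Incremental cost-effectiveness analysis): the cost data are used to "estimate the total costs, set-up costs and program delivery costs per participant for each of the two groups (HIS vs LIS").
- **Where the inputs come from** (Costing surveys, under {18a}): staff of the training organisation and of the university teams fill in forms. For the former, "The costing items for CCIHP should be completed monthly for each CCIHP staff member involved". Under Data management {19}, Cost data, once the forms are verified, "they will be stored with a unique university ID and personnel ID in a folder accessible only to the health economist". No student-level cost is collected.
- **What is randomised** (Sequence generation {16a}): "Within matched pairs, universities will be randomized using a computer random number generator". The pairs are the three regions. The University faculty analysis paragraph confirms that "six universities are assigned to HIS or LIS groups".
- **How uncertainty is handled** (Incremental cost-effectiveness analysis): "Bootstrapping techniques will be used to conduct uncertainty analyses to assess variability in our findings from potential sampling bias". The resampling unit, stratification and interval type are not given, and no variation of unit costs or staff time is described.
- **Costs shared by an arm** (Tables 2 and 3): the pre-implementation webinar and the in-person technical training are each given once per group.

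**The concern.** All men at a university carry the same cost per participant, so the information on how cost varies between sites delivering the same bundle comes from three values per arm. Resampling men within a university cannot move that university's cost. Resampling three universities or three pairs can move it, but a plain percentile interval from three values is known to be too short. Costs incurred once per group have no replication within an arm, so resampling students, universities or pairs cannot reflect their variability.

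The stated purpose is also wrong. A bootstrap estimates sampling variability; it does not detect or measure bias in how the sample arose.

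Aim 4 expects HIS to be cost-effective, and the Introduction and Discussion tie the cost-effectiveness evidence to bringing the programme to scale. For that use, the relevant cost uncertainty is what the bundles would cost at other universities, and this is the part the standard bootstraps understate.

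**Working it through.** **The plan's own counts.** Aim 4 states no interval or power to reproduce. The student counts a bootstrap would draw on do reproduce:
- Men in Table 1: 625 + 600 + 800 + 449 + 1,202 + 1,100 = 4,776.
- Final-wave students: 4,776 x 0.80 x 0.90 = 3,438.7. The power paragraph for Aim 3 agrees: "With a retained sample size of ~3,439 men (4,776 X 0.80 participation X 0.90 retention the final wave").

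**Assumptions not in the documents.** Cost per participant varies normally between universities, with no true arm difference. A coefficient of variation (CV) of 10% to 40% was tried; the results barely depend on it. Retained students are 0.72 x Table 1. The illustrative allocation is universities 1, 3, 5 against 2, 4, 6.

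**1. Students resampled, stratified by university.** Cost is constant within a university and the university sizes are fixed, so every resample returns the same net cost and the bootstrap SE is exactly 0.

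**2. Students resampled, pooled within arm.** With n_i students at university i, N in the arm, p_i = n_i/N, university cost c_i and arm mean m:
- Bootstrap variance of the arm mean = sum of p_i(c_i - m)^2 / N. Only the mix of universities varies.
- True SE of the difference = CV x sqrt(sum of p_i^2 in HIS + sum of p_i^2 in LIS), with mean cost set to 1.
- At CV 20%: bootstrap SE 0.0050, true SE 0.172, ratio 0.0050/0.172 = 0.029. The ratio is 0.030 at CV 10% and 0.029 at CV 40%.
- Approximate coverage of a nominal 95% interval: P(|Z| < 1.96 x 0.029) = P(|Z| < 0.057) = 0.045. Direct simulation at CV 10%, 20% and 30% gives about 4-5%.

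**3. Universities resampled within arm, percentile interval.** Each arm has 3^3 = 27 ordered resamples, of which 10 are distinct; both arms together have 27 x 27 = 729 ordered combinations. All were enumerated over 20,000 simulated trials. Coverage was 81% with normal costs and 81% with lognormal costs. Mean width was 57% of the unpaired t interval on 4 df.

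**4. Three pairs resampled, percentile interval.** The resample that repeats the smallest pair difference three times has probability 1/27 = 3.7%, as does the one that repeats the largest. Both exceed 2.5%, so the limits cannot lie outside the observed smallest and largest pair difference.
- For a symmetric distribution, the chance that this range contains the true value is 1 - 2 x (1/2)^3 = 0.75. Simulation gave 75%, with width 38% of the t interval on 2 df.
- Interpolated percentiles pull the limits inward and give 67%. The protocol does not choose a convention, hence the range 67-75%.

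**5. Small-sample t intervals on the same data.**

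| Interval for net cost | Multiplier | Coverage, normal | Coverage, lognormal |
|---|---|---|---|
| Unpaired t, 4 df | 2.776 | 95.1% | 95.6% |
| Paired t, 2 df | 4.303 | 95.2% | 96.1% |

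These are about 1/0.57 = 1.8 and 1/0.38 = 2.6 times as wide as the matching percentile bootstraps.

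**Not computed.** Coverage for the ICER or net benefit. Both add outcome uncertainty, and the documents do not show how large the cost share would be.

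**The case against.** The strongest reply is that the protocol commits to no particular bootstrap. Resampling unit, stratification and interval type normally belong in an analysis plan, which is not shown. That is fair as far as it goes: silence on these details is no fault. But naming students, universities or pairs with plain percentile limits would not repair the net-cost interval.

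Several stronger readings are tempting and do not stand:
- *That no bootstrap could work.* Only naive student resampling and plain percentile resampling of universities or pairs were examined. Studentised, parametric, wild-cluster and two-stage versions were not, and the protocol's wording does not exclude them.
- *That cost exists only as one figure per university.* The raw forms are kept by staff member, and costs are recorded by activity and phase. Only the derived cost per participant is one value per university. Resampling the forms would still not show how cost varies between universities.
- *That the ICER would look nearly certain.* The figures concern net cost alone.
- *That a student-level bootstrap is illegitimate.* It is a valid statement about student outcome sampling at these six universities. The Aim 3 model itself gives each university its own intercept. The difficulty arises when the result is carried to other universities.
- *That a 2-df pair analysis is the required correction.* Averaging three pair differences is a different estimand from the pooled cost per participant for each group, and pair-wise net effects would set aside the pooled Aim 3 model. The interval may also be very wide. If university totals are similar (CV 5-30%, assumed) and are divided by 0.8 x the Table 1 men, which differ within a pair by as much as 800 against 449, the 2-df interval covers 97-100%, with a median full width of about 200-250% of mean cost. Even so, the range of the pair differences covers only 75%.

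**Conclusion.** The point holds for net cost and for inference beyond the six universities. The protocol fixes the level at which cost per participant is defined and the number of randomised units, and it names bootstrapping as the only uncertainty method. With normal between-university variation, nominal 95% coverage falls to about 4-5% for students pooled within arm (SE zero if stratified by university), about 81% for universities within arm and 67-75% for pairs. The failures differ greatly in degree: student resampling shows almost no cost uncertainty, while university resampling shows some, but too little.

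The small-sample corrections promised in the University faculty analysis paragraph apply to the faculty difference-in-difference models, and nothing comparable appears for Aim 4. The reference to sampling bias is a plain wording error.

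The documents do not support going further, to a claim that bootstrapping must fail or that the ICER interval is wrong by a known amount.

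**What to change.** 1. Report cost per participant for each university and net cost for each matched pair. Give a small-sample university-level interval for net cost, for example t on the three pair differences (2 df) or unpaired (4 df). State that it will be wide and that the pair average is a different estimand from the pooled per-group cost.
2. Show cost uncertainty by varying staff time, unit costs and the set-up share over ranges stated in advance. Include the items delivered once per group, which have no replication.
3. If a student-level bootstrap is kept for the ICER, state that it covers student outcome sampling within these six universities only, and do not use it to support cost-effectiveness at scale.
4. Replace sampling bias with sampling variability in the bootstrap sentence.

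The cost is analysis text and a few tables from data already being collected. The downside is a wider, less favourable uncertainty statement, which reflects what six universities can show.
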